### **8.3 Economic Analysis**

#### *Cost-effectiveness analysis*

The primary analysis will be undertaken at the end of the 4-year follow up from an NHS perspective. All costs and outcomes beyond 1 year will be discounted at 3.5% (NICE, 2013). A broader perspective including women's personal expenditures will be included in a sensitivity analysis. Incremental cost-effectiveness ratios (ICERs) will be computed by comparing the costs and outcomes of the self-management and standard care trial groups. The difference in utility between the two groups will be expressed in terms of QALYs calculated using the UK value set for patient-reported EQ-5D-5L data (Devlin et al, 2018). This will be used in a cost-utility analysis to calculate the incremental cost per QALY gained.

#### *Longer-term decision modelling*

The decision analytic model developed in the main TOPSY trial will be reviewed and updated with data from the 4-year trial measures where appropriate. We will investigate extending the model beyond the original 5 year follow up based on clinical advice on the potential care pathways for women and whether longer term self-management would be recommended.

### **9.4 Trial centres**

Trial centres will remain open with a point of contact for any adverse event reporting or collecting data on any prolapse surgeries that occur during the 4-year follow up. No further information will be collected on women's standard clinic visits.

### **9.5 TSC and DMEC**

The TSC and DMEC, including PPI participants, fully support the 4-year follow up. We will invite all members of the committees to stay involved (although there will be much less oversight required since there is only one additional questionnaire), however we propose at least 1 meeting a year for each of these committees.

## 9.6 Milestones

The milestones below show those of the 4-year follow up and time in months since the start of TOPSY in brackets.

|                             |                 |                                                                                                                                               |
|-----------------------------|-----------------|-----------------------------------------------------------------------------------------------------------------------------------------------|
| Month 1 – 3 (Months 52-54)  | Feb 22-May 22   | All regulatory approvals/agreements, database development/user testing for 4 year outcomes and set up for recruitment of women into extension |
| Months 3-21 (Months 54-72)  | May 22 – Oct 23 | 4 year follow up                                                                                                                              |
| Months 22-24 (Months 73-75) | Nov 23-Jan 24   | 4 year follow up analysis                                                                                                                     |
| Month 24 (Months 75)        | Jan 24          | Dissemination and final reporting.                                                                                                            |

## 10. SAFETY REPORTING

Women will not be asked about adverse events at clinics but TOPSY staff will review all responses in the 4 year questionnaires when they are completed and if any response indicates they may have had a serious adverse event that requires additional reporting we would contact the corresponding centre for more information. Any self reported adverse events noted by the women in the questionnaire which are not serious adverse events will be listed in a spreadsheet. This spreadsheet will be reviewed by the Clinical CI and this has been approved by the DMEC. This includes information on prolapse surgery repair for women who indicate in their response they have had this procedure. All other aspects of safety reporting remain as originally detailed in Section 10.

## APPENDIX E

### **SWAT 86: Advance notification of trial participants before outcome data collection to improve retention – ADAPTED FOR THE TOPSY STUDY**

#### **Objective of this SWAT**

To evaluate the effects of a pre-notification letter or email on completion and return of outcome questionnaires.

Study area: Follow-up, Retention

Sample type: Participants

Estimated funding level needed: Medium

#### **Background**

Many trials struggle with participant retention and completion of follow-up questionnaires. A recent study found that the median (IQR) retention rate across 151 UK trials was 89% (79%-97%). Reminders are generally an effective way of increasing response rates to questionnaires, with some evidence that pre-notification (contacting a participant in advance to say that they will be sent a questionnaire) also provides some benefit, although it is not high certainty evidence. Therefore, there is no clear evidence that pre-notification is effective for trial retention, nor whether any particular method (telephone, text, postcard, letter) of pre-notification confers any benefits over any other, although researchers have reported a lower odds of response following a postcard reminder than following a postal reminder to a survey, albeit after rather than preceding the original questionnaire mailing.

There is also research on the content of contacts with participants, much of which relates to cover letters and post-reminders, although some relates to pre-reminders. Recent research on the content of cover letters by Duncan and colleagues developed a theory-based response letter intervention using Michie's Theoretical Domains Framework (TDF) and associated Behaviour Change Techniques (BCTs). Evidence on the effectiveness of this approach is still inconclusive and has been included as a SWAT idea in the PROMETHEUS project (SWAT24).

It is therefore important to use what evidence is available to develop pre-notification interventions that might improve questionnaire return rates in trials and to evaluate these. Such pre-notifications should be developed using best current evidence in terms of mode of delivery and content, whilst practical considerations should, as ever, also be taken into account in the design and delivery.

This SWAT will test a pre-notification communication sent two weeks before participants are due to be sent their 4-year follow-up questionnaire in the TOPSY study, which is a pragmatic, multi- centre randomised trial testing self-management with clinic-based care for women who use a pessary for prolapse. The intervention to be tested is similar to that in SWAT 76, but will use a letter rather than a postcard in order to provide as consistent a form of pre-notification as possible between participants who opt to complete questionnaires postally and those who opt to complete electronically, whilst maintaining the patient choice of mode of communication.

The text in the pre-notification communication was informed by the theory and associated text used in the IQuad trial SWAT (SWAT 24). The reminder letter (or email) will be personalised to include the (typed) name of the participant because there is some evidence that personalising may improve response rates in surveys.

#### **Interventions and comparators**

Intervention 1: Pre-notification communication in advance of follow-up questionnaire. Participants who elect to complete follow-up questionnaires online will be sent a personalised pre-notification in an email two weeks prior to the mailing of this. Participants who elect to complete follow-up questionnaires in hard copy form and return by post will be sent a personalised pre-notification letter. Similar wording and layout will be used in the email and letter.

Intervention 2: No pre-notification communication.

Index Type: Method of Follow-up

Method for allocating to intervention or comparator

Randomisation

### **Outcome measures**

Primary: Valid response for TOPSY trial primary outcome (yes/no) (i.e. usable outcome data for the primary outcome measure).

Secondary: 1. Valid response for TOPSY trial primary outcome (yes/no) without reminder; 2. Number of reminders sent; 3. Time to response [or ceasing follow-up] (days); 4. Costs per participant retained.

### **Analysis plans**

Baseline participant data, and the primary and secondary outcome measures will be summarised, using frequency (%), mean (SD) or median (IQR), as appropriate) both overall and by SWAT group allocation. For the analysis of the effect of the intervention, all randomised participants will be included in the analysis. Comparison of the primary outcome between the pre-notification letter group and the no pre-notification group will use binary logistic regression, including the randomised group factor and adjusting for stratification variables (TOPSY trial treatment allocation; chosen mode of response). Odds ratios and 95% confidence intervals for the between-groups difference in proportions completing the questionnaire will be estimated, and presented in conjunction with descriptive statistics of the number and percentage of respondents in each group. Analysis of the corresponding secondary outcome (valid response for TOPSY trial primary outcome without reminder) will be performed using the same method.

Time to response will be compared between the groups using Cox regression, adjusted for TOPSY treatment allocation and chosen mode of response. Data will be presented as a hazard ratio and related 95% confidence interval; median time to response in each group will also be presented. For the analysis of the difference in costs per participant retained (i.e. with a valid response for TOPSY trial primary outcome) between those randomised to pre-notification and those randomised to not be sent the pre-notification, costs will include the direct costs of printing the pre-notification letter, envelopes and postage, and the cost of staff time spent administering the mail out (for example filling and labelling envelopes for those who choose to receive questionnaires by post, sending emails to those who choose to receive questionnaires electronically). We will present a crude analysis of the ratio of the estimated between-groups difference in costs, divided by the corresponding difference in proportions providing valid responses for TOPSY trial primary outcome.

A meta-analytic framework will be undertaken by the TOPSY/PROMETHUS team to explore variability across different implementations of the pre-notification SWAT. Proportions of participants responding in each trial of a pre-notification card/letter/text intervention will be entered into a meta-analysis, and the heterogeneity of the intervention effect will be assessed using the I statistic. If substantial heterogeneity is demonstrated (I of 50% or greater), we will explore differences between trials that might explain that variation. The power of any such analyses may be limited if there are small number of trials, but in such an instance we will explore this issue qualitatively using data collected on the trial, the patient population, and the trial context.

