#### **5.4 Retention methods**

Active measures to minimise loss to follow-up of participants include:

- Recording at the outset women's email addresses and mobile phone numbers, their preferred method of contact (for follow up contact) and their preferred method of completion of questionnaires. Questionnaires can be completed online (via an email link) or in paper format and returned by post.
- Participants who do not return their questionnaires within three weeks will be sent up to three reminders using a variety of methods (post/email/ text message dependent on participants preferred method). The third reminder will be by telephone where the researchers will aim to gather the primary outcome data during the call.

Response rates to the self-reported questionnaires will be monitored to ensure they remain above 80%. If response rates are seen to drop, the team will discuss appropriate actions with the Project Management Group. Relevant action may include phone calls at different times of day or asking women to only complete the primary outcome measure.

To facilitate potential long-term follow-up of participants in the trial, women will be asked to consent (in the main trial consent form) to the research team accessing their NHS records via record linkage to ISD data in Scotland and NHS Digital in England. Any further follow up work would only be carried out after relevant regulatory review and approvals.

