## **5 PARTICIPANT SELECTION AND ENROLMENT**

All TOPSY participants who have not withdrawn from the study at the 18-month study time-point will be eligible and will be approached for follow up. All women who have participated in the TOPSY trial will be sent a summary of results newsletter from April 2022. Women were informed they would get this summary of results newsletter in the original participant information leaflet for TOPSY. Alongside this newsletter, a summary results cover letter, patient information leaflet and expression of interest form will also be sent which will include additional information about the 4-year follow up outlining what women are being asked to do i.e. complete one further questionnaire. Women will be invited to opt in should they wish to receive the 4 year questionnaire by either completing and returning the expression of interest form via mail, email or phone call as detailed in the flowchart below. If a woman returns her expression of interest form indicating she would like to complete the 4 year questionnaire, this will be sent on the required date (4 years from when first randomised to the TOPSY study).

Our retention process is the same as that detailed in Section 5.4 with one addition. SWAT 86 has been added for those who OPT in to the 4 year follow up. The SWAT 86 protocol is included as Appendix E. In summary, TOPSY participants remaining in the study 2 weeks prior to the distribution

of their 4 year questionnaire will be randomised to receive a pre-reminder or not to receive a pre-reminder. The mode of delivery of the reminder will be matched to the chosen mode of delivery of the follow-up questionnaire (email for those choosing to respond electronically and post, via a letter, for those choosing to self-complete a hard-copy questionnaire. A more detailed protocol for this SWAT can be found as Appendix E.

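### The cost items listed for SWAT 86 leave out reminders, so the cost per participant retained will be off if pre-notification changes how many are sent

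*Protocol*

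**What the plan says.** Appendix E (SWAT 86) randomises women who opt in to the 4-year follow-up to a pre-notification letter or email, or to none. Its Outcome measures section lists four secondary outcomes. Two matter here: "2. Number of reminders sent" and "4. Costs per participant retained".

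The Analysis plans section of Appendix E contains the only costing definition for the SWAT. It states that "costs will include the direct costs of printing the pre-notification letter, envelopes and postage", and adds "the cost of staff time spent administering the mail out", with envelope filling and emailing as examples. The result is to be a "crude analysis of the ratio of the estimated between-groups difference in costs, divided by the corresponding difference in proportions providing valid responses". No reminder cost is named.

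Reminders continue at 4 years. Appendix D, section 5, says: "Our retention process is the same as that detailed in Section 5.4 with one addition", the addition being the SWAT itself. Section 5.4 allows up to three reminders, by post, email or text according to preference, and "The third reminder will be by telephone", at which researchers try to collect the primary outcome.

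**The concern.** Pre-notification can change resource use in two ways. It costs something to send, and it may change how many reminders are needed afterwards. The listed items capture only the first. The second includes a staffed telephone call. The SWAT treats reminders as something the intervention might affect, since it counts them as an outcome and also has an outcome of valid response without a reminder.

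A cost difference that leaves out a resource which randomisation may change is not the full incremental cost. At stake is whether a secondary outcome meant to tell other trial teams if pre-notification is worth its price can show any offsetting saving or any extra burden. The Possible problems section of Appendix E makes this more than formal. It warns that with high retention there may be little effect to see. If final response can hardly rise, a change in reminders is one of the few remaining ways in which pre-notification could pay for itself, and a small denominator enlarges any error in the numerator.

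**Working it through.** The protocol gives no SWAT unit cost, reminder rate or expected effect, so there is no stated figure to reproduce. The check is algebra, followed by illustrations on assumed values.

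**Definitions** (per woman)
- c_p: cost of the pre-notification.
- c_r: average cost of one reminder.
- dr: mean reminders averted (no pre-notification minus pre-notification).
- dp: gain in the proportion with a valid PFIQ-7 response.

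**Formulas**
- Listed items only: the comparator group has no pre-notification, so the cost difference is c_p and the ratio is c_p/dp.
- Reminders included: the cost difference is c_p − c_r·dr and the ratio is (c_p − c_r·dr)/dp.
- Error in the listed ratio: c_r·dr/dp.

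The listed cost difference is therefore too high if dr > 0, too low if dr < 0, and correct if dr = 0. Any mail-out staff time common to both groups cancels in the difference and does not alter this.

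**Illustration 1: assumed values, in units of one pre-notification (c_p = 1)**

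| dp | c_r | dr | Listed ratio | With reminders |
|---|---|---|---|---|
| 0.05 | 1 | 0.1 | 1/0.05 = 20.0 | (1 − 0.1)/0.05 = 18.0 |
| 0.05 | 3 | 0.1 | 20.0 | (1 − 0.3)/0.05 = 14.0 |
| 0.05 | 5 | 0.2 | 20.0 | (1 − 1.0)/0.05 = 0.0 |
| 0.05 | any | 0 | 20.0 | 20.0 |
| 0.05 | 5 | −0.1 | 20.0 | (1 + 0.5)/0.05 = 30.0 |
| 0.02 | 5 | 0.3 | 1/0.02 = 50.0 | (1 − 1.5)/0.02 = −25.0 |
| 0.02 | 5 | −0.1 | 50.0 | (1 + 0.5)/0.02 = 75.0 |

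**Illustration 2: how dr and dp might move together.** Take an initial mailing plus three reminders, with assumed response of 50% to the mailing and 30% of those remaining at each reminder. Without pre-notification, reminders per woman are 0.5 + 0.35 + 0.245 = 1.095, and final response is 1 − 0.5 × 0.7³ = 0.8285. Let pre-notification multiply the response hazard at every wave, with c_r = 1:
- Hazard ratio 1.1: dp = 0.028 and dr = 0.10. The ratio falls from 36.1 to 32.4.
- Hazard ratio 1.3: dp = 0.070 and dr = 0.27. The ratio falls from 14.2 to 10.3.
- Hazard ratio 0.9: dr = −0.11 and dp = −0.033. The true cost difference is 1.11 against a listed 1, so the listed one is too low.
- Effect only at the last wave (30% to 40%): dp = 0.245 × 0.10 = 0.0245 and dr = 0. There is no error.

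The direction thus depends on what the SWAT finds, and the size on unit costs that the documents do not give.

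**The case against.** A reader might infer that the cost per participant retained is bound to be overstated, and that the analysis could never show pre-notification to be cost-saving whatever the data. The documents do not support that. The costing sentence says what costs will include. It does not say that the list is complete, and nothing excludes reminder costs. Nor does any section say that reminders will fall. The Background to Appendix E finds no clear evidence that pre-notification helps trial retention, and measuring the effect is the purpose of the SWAT. If reminders do not change there is no error, and if they rise the error runs the other way.

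It can also be said that reminder counts will be summarised by SWAT group, so a reader could cost them alongside the ratio. The ratio is openly described as crude, unit-cost detail often sits in an analysis plan, and the planned meta-analysis uses response proportions rather than costs.

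Most of this stands as a limit on direction, size and importance. It does not remove the point. The costing statement is specific down to envelope filling, it is the only one in the document, and reminders are absent from it. An analyst who follows it as written would compute a difference that ignores them. Having the count in a separate table does not correct the ratio.

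**Conclusion.** The point holds in conditional form. If only the listed items are costed, the between-group cost difference equals the pre-notification cost. It is then overstated if pre-notification reduces reminders, understated if it increases them, and right if they do not change. Overstatement is the likely direction if pre-notification speeds response, but that is a hypothesis under test.

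The size cannot be derived from the documents. The illustrations rest wholly on assumed costs and response patterns, and run from no error, through about a tenth of the ratio (36.1 to 32.4), to a change of sign when reminders are dear and many are averted.

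The importance is low. This is the fourth secondary outcome of an embedded retention study, and the host trial's comparison of self-management with standard care is untouched.

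**What to change.** In the Analysis plans section of Appendix E, define cost per woman as the cost of the pre-notification (where sent) plus the cost of every reminder sent, in both SWAT groups. Include post, email and text reminders and the staff time for telephone reminders. Compute the between-group cost difference and the ratio from that. If reminder costs were always meant to be included, one sentence saying so is enough.

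The number of reminders is already a SWAT outcome. The count is needed by type, because a call and an email do not cost the same. Section 5.4 makes the third reminder a telephone call, and the earlier ones follow the woman's preferred method. No further data from participants are required. The cost is a few more unit costs and a small amount of extra costing work.

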### **Possible problems in implementing this SWAT**

Retention to the host (TOPSY) trial for the initial stage of the study was extremely high. We do anticipate a slightly reduced retention rate ( expected from longer term follow up studies), however, if retention rates stay high, there may be minimal effect seen by the proposed intervention.

## APPENDIX F – The APPLE study, a sub-study of TOPSY (Funded Variation to Contract Three)

This annex relates to a sub-study of the main TOPSY trial. In response to an ‘opportunity for additional research call – Dementia and Neurodegenerative Disease’ call from NIHR the TOPSY team developed a feasibility study to explore the possibility of developing an intervention for women who use a pessary for treatment of prolapse and who also have dementia. The acronym for this satellite study is the APPLE study (dementiA and Pessary for ProLapsE).

### Full Study title

Building an intervention to improve the quality of life of women who have dementia and who use a pessary for treatment for pelvic organ prolapse (the APPLE study)

Funding: NIHR HTA (16/82/01) (VTC 03)

Chief Investigator: [name]

### **APPLE Sub-study summary**

|                          |                                                                                                                                                                                                                                                                                                                                                                                                                                                                                                                                                                                                  |
|--------------------------|--------------------------------------------------------------------------------------------------------------------------------------------------------------------------------------------------------------------------------------------------------------------------------------------------------------------------------------------------------------------------------------------------------------------------------------------------------------------------------------------------------------------------------------------------------------------------------------------------|
| Study Title              | Building an intervention to improve the quality of life of women who have dementia and who use a pessary for treatment for pelvic organ prolapse (the APPLE study)                                                                                                                                                                                                                                                                                                                                                                                                                               |
| Study Design             | Mixed methods feasibility study                                                                                                                                                                                                                                                                                                                                                                                                                                                                                                                                                                  |
| Study Participants       | 
In this Annex: Health and social care professionals who care for women who use a pessary for prolapse and have dementia
 
Addressed Elsewhere: Women with dementia and their informal carers will also be part of the study and their inclusion is being considered as part of an application to the Scotland A ethics committee
                                                                                                                                                                                                                                       |
| Planned Size of Sample   | Health and Social Care Professionals: 10-15                                                                                                                                                                                                                                                                                                                                                                                                                                                                                                                                                      |
| Planned Study Period     | 1 September 2022 – 31 August 2023                                                                                                                                                                                                                                                                                                                                                                                                                                                                                                                                                                |
| Research Question/Aim(s) | 
In this Annex
 
 
To understand which services currently deliver pessary care for women with dementia and how those services manage/support the women and their unpaid carers.
 
 
Addressed Elsewhere
 
 
To understand what women with prolapse and dementia and/or their unpaid carers would like from services to treat the woman’s prolapse symptoms.
 
To investigate the feasibility of using routinely collected data to understand the scale of the problem.
 
 |

|  |                                                                                                                                                                                                                                                                                                                                                                             |
|--|-----------------------------------------------------------------------------------------------------------------------------------------------------------------------------------------------------------------------------------------------------------------------------------------------------------------------------------------------------------------------------|
|  | 
 
To develop a team (grant holders, stakeholders and Patient and Public Involvement and Engagement [PPIE] members), who have the necessary expertise, for a future large-scale, robust grant application that will aim to improve the quality of life for women who have dementia and use a pessary for prolapse treatment.
 
 |
|--|-----------------------------------------------------------------------------------------------------------------------------------------------------------------------------------------------------------------------------------------------------------------------------------------------------------------------------------------------------------------------------|

